### Study design

A mixed method study will be carried out, which will compare poorly controlled T2DM patients (poor glycaemic control was defined as an HbA1c value > 9% in the last test performed in the 12 months prior to study inclusion), treated with two different comprehensive approaches with a control group receiving only usual clinical care. The mixed methodology for the development of complex interventions composed of two phases: a first phase consisting of a qualitative study carried out through personal interviews with patients and professionals, and a second quantitative phase that will correspond to the execution of the clinical trial and in which the findings of the first phase will be applied.

We designed this study considering that the intervention group 2 will be the control group for Intervention group 1, where the specific monographic consultation is implemented. Group Intervention 1 includes the main intervention for which we will test the effectiveness to improve glycaemic control. In parallel to Intervention group 2, we decided to include an additional comparison group consisting of type 2 diabetic subjects attending primary care centres managed by our institution in our region, with subjects selected according to the same study criteria. To select this latter group, we describe the use of the Sistema d´Informació per al Desenvolupament de la investigació en Atenció Primària (SIDIAP) database, which contains anonymised electronic health records of patients attended at primary care centers of the same health care districts not participating in the study.

This study is non-randomized because it would be difficult give a different treatment to an individual in the same primary care center treated by the same professional without it affecting the outcome in the standard care arm of the study.

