### Study phases

The INTEGRA study is divided into two distinct phases. Phase 1 is a qualitative research study, which is aimed at identifying viable strategies to overcome barriers to treatment; these strategies have been included in the intervention study (phase 2). Phase 2 is a controlled, non-randomized, interventional, pragmatic study that involves primary care centres in 3 regions in Catalonia (Lleida, Girona and Barcelona).

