##### Inclusion criteria for primary health care Centres

The participating Primary Care centres must meet the following criteria to be eligible: I) experience of more than 5 years using the eCAP™ programme (electronic clinical records of Primary Care Centres in Catalonia) to optimize the use of the software as a source of information and intervention (warnings, alerts, etc.); II) centres with more than 10 general practitioners, to obtain a large number of study subjects; III) centres belonging to different health care areas, to increase external validity of the study; and IV) acceptance by the majority of professionals in the centre.

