#### Control group

The control group will consist of a randomized selection of patients who meet the inclusion criteria and have the same sociodemographic and clinical characteristics as the patients from the intervention groups, including the three participating health care districts. Patients allocated in this group will receive routine clinical care with the usual control by the family doctor and nurse according to the current Catalan Health Institute protocol. The data of patients in the control group will be obtained from the electronic medical record (SIDIAP) database [23]. The inclusion period for the control group will be from 9 December 2015 (the date when the first patient entered the study) until 31 October 2017 (end of the recruiting period). Data on diabetic status, glycaemia and all other study variables that were recorded in the electronic health records for patients in the intervention groups will be extracted from the SIDIAP database for 12 months for each patient. Participants will be followed up until they experience the outcomes of interest, die, leave the SIDIAP database (e.g., change of address) or complete the follow-up (31 October 2018). If the intervention groups reach the study sample earlier than 31 July 2017, the data for the control group will be followed until 12 months from the date when the last patient would be enrolled in the intervention group.

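### Staff acceptance is required of intervention centres but not of the centres supplying SIDIAP controls, so centre willingness is confounded with intervention versus usual care

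*Protocol article*

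**What the plan says.** The centre criteria are introduced with the words "The participating Primary Care centres must meet the following criteria to be eligible" (Inclusion criteria for primary health care Centres). They include a minimum eCAP history ("experience of more than 5 years using the" system), a size threshold ("centres with more than 10 general practitioners, to obtain a large number of study subjects") and "acceptance by the majority of professionals in the centre".

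The usual-care comparator is defined elsewhere. Study design places it in "primary care centres managed by our institution in our region, with subjects selected according to the same study criteria", and specifies anonymised SIDIAP records of "patients attended at primary care centers of the same health care districts not participating in the study". The Control group section describes a "randomized selection of patients who meet the inclusion criteria and have the same sociodemographic and clinical characteristics as the patients from the intervention groups". Neither section states a criterion for the control centre itself beyond institution, district and non-participation.

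Allocation is openly not random: "Phase 2 is a controlled, non-randomized, interventional, pragmatic study" (Study phases). The Statistical analysis plan section checks baseline balance on age, socio-demographic factors, comorbidities, laboratory values, medication and complications. If patient characteristics differ, it plans a regression or propensity-score adjustment. It names no centre-level variable.

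**The concern.** The interventions target clinical inertia, which is a behaviour of professionals. A centre whose staff mostly agree to join such a project may already intensify treatment differently from a centre for which agreement was never required. If so, part of any difference between an intervention group and the SIDIAP group existed before the intervention started.

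The comparison matters. The hypothesis under Aims of the study is framed against usual practice. The secondary aims on lipids, blood pressure, complication screening, direct costs and behavioural risk factors are framed against the control group, and only the SIDIAP group represents usual practice. The Discussion acknowledges that patients who volunteer tend to be more motivated, but says nothing of centres that volunteer.

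**Working it through.** **Step 1: set the requirements side by side.**

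| Attribute | Centres of IG-1 and IG-2 | Centres supplying SIDIAP controls |
|---|---|---|
| Agreement of most professionals | Required | Not stated; must be non-participating |
| More than 10 GPs | Required | Not stated as a criterion (see step 2) |
| More than 5 years of eCAP | Required | eCAP use implied, because the Discussion says SIDIAP holds eCAP data; the 5-year minimum is not stated |
| Same institution and districts | Yes | Yes |
| Level at which patients are selected | Patients within accepting centres | Patient criteria and characteristics |
| Level of balance check and adjustment | Patient | Patient |

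The first row carries the point. Acceptance holds for every intervention centre and is required of no control centre, and no planned analysis variable represents it.

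**Step 2: check whether another section closes the gap.**

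- Study setting has health areas chosen to be alike and organised into IG-1, IG-2 and control.
- Sample size calculation gives each group, control included, three basic health areas averaging 10 care units.
- Evaluation of the effectiveness in the three study groups speaks of three types of centre.
- Intervention design puts two intervention groups and a control group inside each basic health area.
- Study design and Control group describe a patient draw from the database, and Study design confines it to non-participating centres.

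The first three suggest defined control areas of comparable size. The fourth gives a different layout, and the last does not mention control areas. So comparability of size is suggested but not fixed. None of these sections addresses acceptance.

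**Step 3: which contrasts are affected.** Centres in IG-1 and IG-2 both fall under the participating-centre criteria, so that contrast is not touched. IG-1 versus SIDIAP and IG-2 versus SIDIAP are.

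**Step 4: size.** The article gives no centre-level difference in HbA1c change, so the bias cannot be computed. An illustration can be built on the sample-size inputs, which reproduce:

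- Unadjusted n per group for a 1-point difference, SD 1.46, two-sided 0.05, power 80%: 33.46.
- With 20% loss: 33.46 / 0.8 = 41.8, rounded to 42.
- Design effect: 1 + (15 − 1) × 0.05 = 1.7.
- 42 × 1.7 = 71.4, rounded to 72; 72 × 3 = 216 per group; 72 × 9 = 648 in total.

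With 216 × 0.8 ≈ 173 evaluable per group, SE = 1.46 × √(2/173) = 0.157. With the design effect, SE = 0.157 × √1.7 = 0.205. Suppose the intervention has no effect and the centres already differ by b. The chance of a significant result is 1 − Φ(1.96 − b/SE) + Φ(−1.96 − b/SE).

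| Assumed b (HbA1c points) | Share of 1-point target | Unclustered test | With design effect 1.7 |
|---|---|---|---|
| 0.1 | 10% | 10% | 8% |
| 0.2 | 20% | 25% | 16% |
| 0.3 | 30% | 48% | 31% |

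The nominal rate is 5%. More patients would not reduce b; they would only make it more likely to be declared significant.

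**The case against.** The strongest reply has four parts.

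1. **The article does not describe an unrestricted control pool.** A reader might infer that controls come from any centre, including those that declined and those too small to qualify. The text does not support this. The pool is limited to the same institution and districts. No section reports a refusal or says that declining centres supply controls, although none excludes them. The sections describing similar control areas averaging 10 care units point away from a size imbalance, and drawing patients at random within chosen control areas would be compatible with them. This stands: size confounding is unresolved, not established. An eCAP contrast is weak too, since SIDIAP is built on eCAP records.

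2. **The main comparison is elsewhere.** Study design names IG-2 as the control for IG-1 and calls the SIDIAP group additional. This also stands and limits the reach of the point, but the hypothesis and several secondary aims still rest on usual care.

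3. **Patient-level adjustment may absorb part of the difference.** The outcome is a change from baseline, and medication and laboratory values are among the variables checked. Treatment at a given HbA1c partly reflects past intensification. That is fair, but these variables do not measure staff readiness and cannot be relied on to remove its effect.

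4. **A condensed article leaves extraction rules to the full protocol.** That covers detail. It does not cover a control source that the article itself fixes and describes in conflicting ways.

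**Conclusion.** The point holds for centre willingness. Acceptance is a condition of entry for intervention centres and is not required of control centres, and the planned checks and adjustment stay at patient level. IG-1 or IG-2 versus usual care is therefore confounded with it.

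The conclusion goes no further than that. Confounding by size awaits reconciliation of the text, use of refusing centres is permitted but not stated, and IG-1 versus IG-2 is unaffected. The size of the bias is unknown. The 0.1 to 0.3 point range is an assumption with no source in the article, and the false-positive rates above depend on it, on the SD of 1.46 and on 173 evaluable patients per group. The design should be amended for the usual-care comparison; the study as a whole is not invalidated.

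**What to change.** 1. Reconcile Study design, Study setting, Intervention design, Control group and Sample size calculation so that they give one account of which centres supply the controls.
2. In Control group, restrict the SIDIAP draw to centres meeting the same objective criteria: more than 5 years of eCAP and more than 10 GPs. Centre identity must already be usable, because participating centres have to be left out of the draw.
3. Pre-specify a sensitivity analysis. For patients meeting the study criteria in intervention and control centres, extract the 12-month HbA1c change from the period before 9 December 2015, and report the usual-care contrast net of that pre-period difference. State that it covers all eligible patients, not consenting volunteers, so it supplements the main estimate and cannot replace it.
4. State residual centre willingness as a limitation of the usual-care comparison. Restricting the draw on size and eCAP does not remove it. Nor would excluding centres known to have declined, because the willingness of centres never approached stays unknown.

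The cost is a narrower query, one historical extraction and some redrafting. The control-centre pool becomes smaller, by an amount the article does not allow one to judge, and the interval on the pre-period-corrected estimate becomes wider.

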### Study setting

This mixed method study will be conducted in primary care settings in 3 different health care territories of the Catalan Health Institute (Lleida, Barcelona, and Girona). Each basic health care area will be selected with similar characteristics and will be organized into the intervention group 1 (IG-1), the intervention group 2 (IG-2), and a control group.

### Characteristics of participants

The inclusion criteria include the following: T2DM of more than one year of disease duration, age between 30 and 80 years, HbA1c > 9% in the last test performed in the 12 months prior to study inclusion, with no change in antidiabetic treatment within the previous 3 months. The changes in the dose of a drug in the antidiabetic treatment will be not considered as exclusion criteria.

The exclusion criteria include the following: T2DM controlled by endocrinologist at the moment of inclusion, systemic glucocorticoid treatment (ATC code: H02AB) or orlistat treatment (ATC code: A08AB01) (chronic or during the two months prior to inclusion), estimated life expectancy < 2 years, active treatment for malignancy (other than basal cell cancer or squamous cell skin cancer), serious mental disorders (psychosis, bipolar affective disorder, severe depressive episode with psychotic symptoms), class III or IV (New York Heart Association functional classification) heart failure (ICD-10: I50), dementia, renal transplantation or current dialysis treatment, history of drug and/or alcohol abuse (ICD-10: F10-F14), pregnancy or lactation, treatment with immunosuppressive drugs, haemoglobinopathies (ICD-10: D58.2), or chronic anaemia, body mass index (BMI) > 45 kg/m^2^, or any conditions that the investigator considered could prevent the patient from completing the study.

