##### Study variables

The variables are collected at different time-points during the study (Table 1). These include: sociodemographic variables (age, sex), anthropometric variables (height, weight, BMI, blood pressure), clinical variables (drugs and dosages), smoking habits (smoking, non-smoker, ex-smoker), presence of multiple disorders (Clinical Risk Group and identified in the computerized patient clinical history and the number of health problems as a proxy asset of multi-morbidity), presence of microvascular complications (diabetic retinopathy, diabetic nephropathy, and diabetic neuropathy), presence of macrovascular complications (ischaemic heart disease, stroke, peripheral vascular disease, and heart failure), laboratory variables according to the standard procedures of the laboratory of reference (HbA1c, blood count, renal function- creatinine, glomerular filtration rate, urinary excretion of albumin), liver function (Alanine Aminotrasferase (ALT), Aspartate Aminotransferase (AST), alkaline phosphatase, Gammaglutamil transferase (GGT)), lipid profile (total cholesterol, HDL-C, triglycerides, LDL-C, and non-HDL-C), and episodes of severe hypoglycaemia (episodes of hypoglycaemia that require the intervention of a third party for recovery will be recorded).

**Table 1 Tab1:** Study timeline, variables and procedures

	IG-1 and IG-2					Control group	
Data collected	Assessment (months)				Source	Assessment	Source
	0	3	6	12		Month 0 & Month 12	
Inclusion/Exclusion criteria	1 + 2	1 + 2	1	1 + 2	e-CRF	§	SIDIAP
Sociodemographic variables and comorbidities: *1. Age, height, gender, weight, BMI, duration of T2DM, medication (active component and dose),* etc.*...* *2. Pluripathology, clinical risk group*	1 + 2	1	1	1 + 2	eCAP	§	SIDIAP
Main variable: HbA1c	1 + 2	1	1	1 + 2	e-CRF eCAP	§	SIDIAP
Lipid profile and other laboratory variables: Total cholesterol, HDL, LDL, triglycerides, non-HDL, urea, creatinine, glomerular filtration rate, urine albumin, AST, ALT, FA, GGT. Systolic and diastolic blood pressure	1 + 2	1	1	1 + 2	eCAP e-CRF	§	SIDIAP
Smoking habit	1 + 2	1	1	1 + 2	eCAP e-CRF	§	SIDIAP
Sedentary lifestyle	1 + 2	1 + 2	1	1 + 2	e-CRF		
Detection of macrovascular complications *Ischaemic heart disease, stroke, peripheral artery disease, heart failure*	1 + 2	1	1	1 + 2	eCAP e-CRF	§	SIDIAP

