Chronic microvascular complications detection *Diabetic retinopathy, diabetic nephropathy (albuminuria, renal failure), diabetic neuropathy*.	1 + 2	1	1	1 + 2	eCAP e-CRF	§	SIDIAP
Costs: *Cost of medication, laboratory tests, additional tests, cost of staff (visits), referrals, IT*	1 + 2			1 + 2	eCAP e-CRF	§	SIDIAP
*Costs:* *Urgent care, outpatient and hospital admissions*	1 + 2			1 + 2	e-CRF		
Satisfaction and quality of life of patients *DTSQ / ESDQoL*	1 + 2		1	1 + 2	e-CRF		
Professional Satisfaction *Specific Questionnaire*				1 + 2	e-CRF		
intensification/treatment adherence		1 + 2	1	1 + 2	e-CRF		
Occurrence of severe hypoglycaemia episodes	1 + 2	1	1	1 + 2	e-CRF		SIDIAP
“Patient Activation Measure” questionnaire (instrument for disease self-evaluation)	1 + 2	1 + 2		1 + 2	e-CRF		

*For the IG-1 (monographic + training of professionals + additional measures originated in phase 1), clinic visits will be carried out at baseline, 3, 6, and 12 months. For the IG-2 (training of professionals + additional measures originated in phase 1), clinic visits will be carried out at the time of inclusion (month 0), 3, and 12 months*

Variables related to healthcare costs are also collected and include the costs derived from the medication used (cost per patient per month of medication prescribed according to prices set by the Health Ministry), laboratory tests used (based on prices listed in the Catalan Health Institute service portfolio), supplementary tests, professional costs (the cost of patient visits), cost derived from the referrals to specialists, use of the emergency department, outpatient and hospital admissions, temporary disability, and consumption of testing strips for measuring blood glucose.

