### Statistical analysis plan

For data analysis, the IG-1, the IG-2, and the control group will be compared. All analyses will be carried out using bilateral tests with a nominal significance level of 0.05. However, if the comparisons obtain a *p*-value of less than 0.10, they will also be discussed as indicative of trends. Initially, basal characteristics of all groups will be evaluated to establish homogeneity in age, socio-demographic, comorbidities, laboratory parameters, concomitant medication and diabetes complications. An initial, descriptive comparison between groups of all variables will be performed to evaluate their baseline balance. Statistical significance will be assessed by the chi-square or t-test between the groups. Exploratory analyses will be applied when necessary.

The main variable is set as the difference in mean HbA1c values between the final visit and baseline. The difference will be evaluated in terms of the evolution of HbA1c as contrasted between groups by paired t-Student, or if the assumption of normality is not met for the right non-parametric.

If differences in the characteristics of the patients in each group are observed in the descriptive section of the study, a linear regression of the main variable (parameter evolution during the study) will be adjusted. This linear regression adjusted for the variables identified in the descriptive section, or the ability to adjust the model by setting a propensity score, will be evaluated. For all models, the distribution of waste will be studied, as well as the coefficient of determination (R2), to check for the correct setting.

As was done in Vinagre et al. [4], a subgroup analysis will be performed by a) gender (male / female), b) age: < age 65 / ≥ 65, and c) according to HbA1c control levels (< 10% / ≥ 10%).

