## Discussion

According to the SIDIAP database, which contains all the data entered into the eCAP, the database used in Catalan Health Institute, 79.6% of the patients have HbA1c values ≤8%, and the proportion of patients with fair control (HbA1c ≤7%) is 56.1% [4].

The INTEGRA study defines potential pragmatic new strategies to improve metabolic control in patients with very poorly controlled T2DM in the primary care setting that, if demonstrated to be effective, could be implemented by professionals in their real-life practices at ICS. The research team agreed to define poorly controlled T2DM patients as those who had HbA1c levels ≥9%. This is because at the time of the protocol writing, local and international guidelines were recommending the initiation of insulin therapy in type 2 diabetes when HbA1c levels were between 8.5 and 10% [32, 33]. Due to this the lack of agreement, the ≥9% cut-off was chosen in accordance with the AACE Comprehensive Diabetes Management Algorithm 2013 [34], which is actually a value in between all recommendations. Moreover, our population characteristics and primary health care patterns of treatment were taken in account. Indeed, those subjects with HbA1c levels > 9% are usually the ones that most often need to be treated with insulin, but this therapy is frequently delayed or not even started by some general practitioners in our primary health-care centres [4]. Some studies report that a multifactorial target intervention used for the management of T2DM is effective and feasible in clinical practice. An intensive intervention strategy delivered at the clinical level is associated with a significant and durable improvement in HbA1c and major cardiovascular risk factors, well beyond that achieved with the usual practices [35]. Some studies describe that patient-centred care is more valuable when targeted to patients with HbA_1c_ > 8.5%. Patient-centred care was most effective and cost-effective in those patients, resulting in more improved glycaemic and metabolic control but also improving quality-adjusted life years and costs of associated complications [36].

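### Month 0 is not tied to the qualifying HbA1c in the same way in all groups, so regression to the mean could enter the contrasts with usual care unequally

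*Protocol article*

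**What the plan says.** - **Selection.** Under Characteristics of participants, a patient qualifies on "HbA1c > 9% in the last test performed in the 12 months prior to study inclusion". The same list also asks for a period of stable therapy, worded as "with no change in antidiabetic treatment within the previous 3 months". Dose changes do not exclude.
- **Outcome.** The Statistical analysis plan section states: "The main variable is set as the difference in mean HbA1c values between the final visit and baseline". Regression or propensity-score adjustment is foreseen only if the descriptive comparison shows differences between groups.
- **Month 0 in the intervention groups.** In Table 1 the row "Main variable: HbA1c" has a month-0 entry for IG-1 and IG-2, sourced from the e-CRF and eCAP. The table note says for IG-1 that "clinic visits will be carried out at baseline, 3, 6, and 12 months" and for IG-2 that "clinic visits will be carried out at the time of inclusion (month 0), 3, and 12 months". The Data collection section says that laboratory variables in these groups come from the clinical history and anamnesis.
- **Month 0 in controls.** All control data come from SIDIAP. The Control group section says "The inclusion period for the control group will be from 9 December 2015" and runs that period to 31 October 2017. It gives no rule for an individual control's month 0.
- **Three-group comparison.** The section on effectiveness in the three study groups limits it to SIDIAP variables and promises time windows for accepted values, without giving them. It leaves open whether the comparison is a cohort or two cross-sectional surveys.

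**The concern.** Selecting on one high value means that the next test will on average be lower with no treatment at all. A change score counted from the selecting test contains that whole fall. A change score counted from a later test has already shed it. This is harmless between groups if baseline stands in the same relation to the selecting test in every group, but the article does not secure that. In the intervention groups there is an inclusion visit at which a new test could be taken, up to 12 months after the qualifying one. In controls there is no visit, and the qualifying record is an obvious candidate for month 0.

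At stake is the comparison with usual care, which is how the hypothesis is framed and which several secondary aims use. A fresh baseline in the intervention groups against the qualifying value in controls would make controls appear to improve more and hide a benefit. The reverse would create a false one. The 3-month rule on antidiabetic treatment does not close the gap, because the qualifying test may be up to 12 months old.

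**Working it through.** **The plan's own figures first.** Two-sided alpha 0.05, power 80%, difference 1 point, SD 1.46: n = 2 × [1.46 × (1.960 + 0.842)]² = 33.5, so 34 per group. Allowing for 20% loss, 34/0.8 = 42.5; the article uses 42. Design effect: 1 + (15 − 1) × 0.05 = 1.7. Then 42 × 1.7 = 71.4, rounded up to 72, and 72 × 9 = 648. The stated figures reproduce, and 1 point is the yardstick.

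**Where the artefact comes from.** Let Q be the mean qualifying value, R the mean of a re-test at month 0 and M the mean at month 12, all without treatment effect and equal in both arms. If controls are measured from Q and intervention patients from R, the changes are M − Q and M − R. Their difference, intervention minus control, is Q − R. Swapping the baselines reverses the sign.

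**Source distribution.** The Discussion gives, for SIDIAP patients: "79.6% of the patients have HbA1c values ≤8%, and the proportion of patients with fair control (HbA1c ≤7%) is 56.1" per cent. Fit a normal distribution to these two points:
- z(0.561) = 0.1535 and z(0.796) = 0.8274
- SD = (8 − 7)/(0.8274 − 0.1535) = 1.484
- mean = 7 − 0.1535 × 1.484 = 6.772

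**Mean of those above 9%.**
- a = (9 − 6.772)/1.484 = 1.501
- density 0.1293, upper tail 0.0666
- excess over the population mean = 1.484 × 0.1293/0.0666 = 2.88
- mean above 9% = 6.77 + 2.88 = 9.65

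**Expected fall on re-test.** Q − R = (1 − r) × 2.88, where r is the correlation between the qualifying and month-0 tests. The article does not give r; the values below are assumptions. The first column of points supposes that every patient in one arm has a fresh baseline and every patient in the other has the qualifying one. The second supposes that only half of the fresh-baseline arm has one.

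| r | All affected | Half affected |
|---|---|---|
| 0.9 | 0.29 | 0.14 |
| 0.8 | 0.58 | 0.29 |
| 0.7 | 0.86 | 0.43 |

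A log-normal fit to the same two percentages, with r applied on the log scale, gives 0.33, 0.65 and 0.97 for the middle column.

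**Effect on the test, all affected.** With 216 per group, the effective size is 216 × 0.8/1.7 = 101.6, and the standard error is 1.46 × √(2/101.6) = 0.205. With no true effect, an artefact of 0.29 raises the two-sided rejection rate from 5% to about 29%, and 0.58 raises it to about 80%. If 0.58 runs against the intervention, power for a true 1-point effect falls to about 54%.

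**The case against.** The strongest reply is that no re-test is documented. Table 1 shows that a month-0 value is recorded, not that blood is drawn. The Data collection section takes laboratory values from the clinical history, which fits using the last recorded result, that is, the qualifying test. Controls are said to be selected by the same criteria. If the last record before inclusion is the baseline everywhere, regression to the mean is broadly equal. This stands, and it is why the point is a risk only.

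Second, the three-group comparison is confined to SIDIAP variables, and the Discussion says that SIDIAP holds all data entered in eCAP, so one record system serves all groups. This stands as to source. It does not settle which test is baseline, because a test taken at the month-0 visit would be in the same system.

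Third, the promised windows may resolve it, and a condensed article need not print them. They may. But the article itself fixes the selecting test, the change outcome and a month 0 that arises differently by group, and a window of any width does not by itself put every group on the same side of the selecting test. Adjustment that depends on observed imbalance does not repair a baseline defined differently by group.

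Fourth, the Study design section names IG-2 as the control for IG-1 and the SIDIAP group as an additional comparison. Both intervention groups have a month-0 visit, so that contrast is largely spared. This stands and limits the scope.

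A reader might infer more: that the intervention groups are in fact re-tested, that the control baseline is in fact the qualifying value, or that the lag from qualifying test to month 0 in fact differs between arms. The article supports none of these. It gives no lag for any group, and the 12-month limit is common to all.

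**Conclusion.** The point holds as a gap in how baseline is fixed, not as a demonstrated bias. The article combines selection on a single high HbA1c, a change-from-baseline outcome and a month 0 that is not anchored to the qualifying test in the same way in every group. If the baselines differ, the contrasts of IG-1 and IG-2 with usual care carry an artefact of up to 0.29 to 0.86 HbA1c points for r between 0.9 and 0.7, that is, 29% to 86% of the 1-point design difference, in a direction that cannot be told from the text.

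Those figures are an upper bound. They rest on an assumed r, on a distribution extrapolated from cut-points at 7% and 8% to the tail above 9%, and on every patient being affected. They should not be read as the expected bias. If the qualifying value is baseline in all groups, the artefact largely cancels.

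**What to change.** For the contrasts with the SIDIAP control only, state before the data are extracted:

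1. Baseline HbA1c is the qualifying value in all three groups: the last eCAP/SIDIAP result before the index date. The index date is the inclusion visit in IG-1 and IG-2.
2. Each control is assigned an individual index date within the inclusion period, with eligibility judged at that date. Dates are drawn so that the lag from qualifying test to index date has the same distribution as in the intervention patients, for example in 3-month bands.
3. Month-12 HbA1c comes from the same record source and the same window around index date plus 12 months in all groups. This requires the cohort option, not two cross-sectional surveys.
4. The analysis is a regression of month-12 HbA1c on group, adjusted for qualifying HbA1c and lag, whether or not the descriptive comparison shows an imbalance.

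A month-0 test, where one exists, can remain the baseline for IG-1 versus IG-2 if both groups have it.

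The cost is analysis-plan wording and extraction work. No new data are needed and care does not change. A qualifying value that may be months old predicts month 12 somewhat less well than a fresher test, so a little precision is lost.
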